### **Corresponding author:**

[name], Clinical Senior Lecturer, Institute of Applied Health Research, College of Medical and Dental Sciences, University of Birmingham, [name]

[[contact]](mailto:[contact]), (registered on BMJ site as [contact])

[contact]; [contact]

**Summary of 2-year follow-up protocol:** The Gambia has high rates of under-5 death from diarrhoea and pneumonia that peak during the weaning age. Community-based interventions may reduce weaning-food contamination and disease rates. A clustered randomised controlled trial was conducted in the Central River Region of the Gambia in 2012-15 to trial a community level weaning-food safety and hygiene intervention.

The initial registered protocol outlined a 6-month follow-up. A random sample of 30 villages (clusters) with a population of 200–450 was selected and after a baseline survey clusters were randomly assigned using a random number table within strata 1:1 to either – four intensive days of a community level campaign like intervention to improve weaning-food hygiene practices plus a reminder visit at 5 months, delivered through traditional Gambian performing arts and the existing public health and village structures – or to a one day community intervention campaign for use of water in domestic gardening in the control arm. The primary outcome was a composite score of five key food-related hygiene behaviours (observed), hereafter called 5-behaviours. Secondary outcomes included microbiological contamination of food and water for child's consumption; the prevalence of diarrhoea and respiratory diseases; and mothers' reporting of diarrhoea admission. Outcomes were measured at 6 months after the intervention in a cross-sectional survey of 20 randomly selected mothers with a child aged 6–24 months per village. Outcomes were compared in an intention-to-treat analysis between intervention and control group adjusted for mother's age, mother's education, sex of the index child, and number of children in the household.

Further funds were secured to follow-up to assess the ongoing effect of the intervention 2 years after the 5th month reminder visit. There have been no further contact with the villages after the 6-month follow-up. Methods will be similar to the 6-month follow-up. Outcomes will be measured in a cross-sectional survey of 26 randomly selected mothers with a child aged 6 to 36 months per village. The same primary and secondary outcomes measured in the

6-month follow-up will be measured at 2 years with the addition of assessing the effect of the intervention on hospitalisation from acute respiratory tract infections (ARI) and health economics analysis of ARI for the child, family-food behaviour and diarrhoea outcomes, qualitative studies. There will also be two nested cross-sectional studies examining the degree of agreement between two methods of measuring microbiological water quality and the play and care-giving behaviours related to contamination of toddler's hands outside in the yard.

**Trial registration:** The trial was registered on the 17th October 2014 with the Pan African Clinical Trial Registry in South Africa with number PACTR201410000859336.

**Keywords:** cluster randomised controlled trial, diarrhoea, pneumonia, behaviour change, weaning-food, hygiene, food preparation, community intervention, performing arts, dramatic arts, motivational drives, scalability, Africa.

## **Important Note:**

To avoid repetition and for ease of reference to the original protocol the 6-month cRCT original protocol is copied below (<https://clahrcwmblog.files.wordpress.com/2017/06/protocol-[name]-et-al-promoting-hygienic-weaning-food-handling-practices-2017-ver1-2.pdf>) and this is followed by the 2-year follow-up details where different from the 6-month protocol.

During the 6-month follow-up there were no deviations from protocol. Minor changes after registration of the trial took place, but these were before the start of intervention and evaluation fieldwork. These included: addition of the secondary outcome ‘diarrhoea hospitalisation in the last episode’; and collection of cost data for child’s diarrhoea disease.

## **1. Protocol for 6-month follow-up of communities in the cRCT investigating the effect of weaning-food hygiene community intervention in rural Gambia.**

### **1.1 Background**

Two small proof of concept individually randomised efficacy trials (in Mali and Bangladesh) used Hazard Analysis and Critical Control Points (HACCP) to identify critical control points for improving weaning-food hygiene and related mother’s behaviour inculcated in a programme of individual training and follow-up of mothers. A recent community intervention conducted in Nepal successfully tested such interventions as part of a community mobilisation intervention using the motivational behaviour change model (based upon research in psychology that proposes ways of classifying various drivers of human behaviour) in a before-and-after cluster study. The former study was too intensive to

be scalable, while the latter needs to be evaluated in a larger trial and further simplified for scaling up in size.

We describe here the design of a complex public health community intervention for our cluster-randomised control trial (cRCT). The primary objective of the trial was to investigate the effects of the complex public health community intervention that sought to improve mothers' weaning-food hygiene practices, and further to investigate the effect of the intervention on the level of microbiological contamination in food and water ready for child's consumption, the prevalence of diarrhoea and respiratory symptoms, and diarrhoea admission, as reported by the mothers.

## **1.2 Methods:**

### **1.2.1 Design, setting and population**

The cRCT was conducted in the Central River Region (CRR), one of the seven administrative regions in the Gambia with a total of 659 villages, and a population of 201,506 of which 41,334 (20%) are under-5 years olds. CRR was selected as it has the highest incidence of diarrhoea in the Gambia, particularly in children aged 6–24 months (26.5% of children under-5 had diarrhoea in the two weeks preceding the UNICEF Multiple Indicator Cluster Survey (MICS) in 2010, verses 17% nationally. The rates for ARI of children under-5 were 14.2% in CRR compared to 6% nationally). As with other regions, UNICEF and the Ministry of Health and Social Welfare (MOH) have selected a number of villages (158 in CRR) to become Primary Health Care villages where they have trained (for four weeks) a Village Health Worker (VHW) and a Traditional Birth Attendant (TBA) to provide health promotion and basic health support to the villagers.

Inclusion criteria for study villages were Primary Health Care villages with a population of 200–450 within CRR. Exclusions for the villages were those that were within 5km of already selected villages.

Inclusion criteria for households within the selected villages for baseline were mothers with children aged 6-24 months expecting to be resident in the village for the following six months. There were no other exclusions. Inclusion criteria for households for the evaluation of the intervention were mothers with children aged 6-24 months at the time of the four day visit of the intervention team to their village. Exclusions were the unavailability of the index child's main carer for cooking the index child's weaning-food during the evaluation visit.

### **1.2.2 Intervention**

The intervention components and delivery package were theory-based (HACCP promoted by WHO/FAO Expert Committee on Food Safety and the motivational behaviour change model), informed by local context from our formative research, and lessons/tools from community interventions in studies on hand washing in India and weaning-food hygiene in Nepal. Our formative research found critical control points for weaning-food hygiene behaviour change in mothers (Table 1) and that Nurture, Disgust, Affiliation, Status and Purity were the strongest motivational drives for our village mothers.

For its delivery, we focussed on the use of performing arts (using culturally engrained styles of drama and songs), competitions and environmental cues to deliver the HACCP corrective measures and motivational drives. The details of our community weaning-food hygiene programme, designed by the research team at the University of Birmingham (including a Gambian Public Health officer from MOH), underwent wide consultation with expert health promotion agencies represented on a Local Scientific Advisory Committee in the Gambia.

Subsequently, the material was translated into the three local languages, field-tested and piloted iteratively by the intervention team in the CRR. This team, which also delivered the programme, consisted of one literate male and one illiterate female traditional communicator (cultural artists/musicians/drummers) with health promotion experience, three Public Health Officers (PHO) and an illiterate driver. The team were assisted by a female volunteer (usually a TBA) from each village, trained for two weeks, to assist during and in between the team visits. They were encouraged to find more assistant volunteers called *MaaSupervisors*.

The intervention focussed on a central role model character the “*MaaChampion*”, a mother, who practises the key behaviours used in the messages (Table 1) and encourages other mothers to do the same. Village mothers could achieve “*MaaChampion*” status if they demonstrated the same. Other components such as competitions (for mothers of children <5 years) and environmental cues were designed to embed behaviour change. The intervention was delivered to the entire population but focussed on mothers with children under-5 years in each village. It consisted of the team visiting each village on days 1, 2, 17 and 25, delivered between February and April 2015 (the dry season). A fifth visit took place after six months since we envisaged that if such a programme is to be implemented at scale, then to sustain behaviour change, villages would need a reminder visit before or early in the diarrhoea high-risk rainy season (if several months after the initial four day campaign), a time when mothers and their families are busy with farm work and may forget weaning-food hygiene behaviours. The programme’s daily schedule is summarised in Tables 2.

Implementation was staggered over two months. The intervention team logged significant events, comments and overall participation of villagers/mothers in the programme that helped guide the process evaluation of the intervention implementation.

The control villages were given a day's health education campaign on water use in domestic vegetable gardening. A public health officer held community meetings explaining the campaign using a flipchart.

### **1.2.3 Outcome data collection**

Evaluation of outcomes took place six months after the last of the four day village visits during the high-risk rainy season. We hypothesised that if families were to retain the weaning-food practices learnt six months earlier, during this busy and high-risk period of the year, then our intervention would be successful. Independent newly recruited female data collectors received training for data collection. They moved in a group visiting one village per day and for each village one data collector was assigned to a mother who they observed for the day from approximately 6am-3pm.

An observation checklist was designed to collect data on mothers' food hygiene practices. As the baby food is made at the same time as family breakfast, the practices were those for preparing morning's food. Questionnaires were piloted and were used to collect data on the background characteristics of each family, the mother and child, data on income, health education related knowledge, the incidence of diarrhoea, ARI and hospitalisation for the index child, plus other questions that acted as diversions.

### **1.2.4 Food and water sampling**

Data collectors collected food and water samples aseptically using the methodology described by Islam et al. Samples were collected from weaning-food: i) immediately after the morning preparation before feeding the index child, ii) after storage (minimum three hours) and prior to feeding the index child. Water ready for drinking by the index child was also sampled.

### **1.2.5 Outcomes and outcome measures**

The primary outcome was the observed difference between the arms in the mean proportion of all five key food-related behaviours (Table 1) versus all opportunities for performing the behaviours during the observation period (6am–3pm by female data collectors) (hereafter called *5-behaviours*). The other outcomes were:

- (1) Microbial (total coliform) growth from weaning-food after making and after storage, and from water, before being consumed by the infant.
- (2) Presence of any days of diarrhoea (three watery stools in 24 hours) over the past seven days reported by the mother.
- (3) Presence of any days of ARI (cough with difficulty breathing) over the past seven days reported by the mother.
- (4) Reported hospital admission as the result of the last diarrhoea episode.
- (5) The mean proportion of each individual food hygiene practices (including boiling water behaviour not a part of food hygiene behaviours) versus all opportunities for performing each behaviour during the observation period (6am–3pm).

### **1.2.6 Sample size**

Observations during the formative research indicated that the population proportion of events in which correct behaviour was displayed (i.e. practices of heating of stored food, hand washing with soap before food preparation, during food preparation if contaminated, and before feeding the baby (measured in the first time activity occurred)) was 17/150 (11.3%). For the sample size calculation, we assumed an intra-cluster correlation coefficient (ICC) of 0.04 between villages and a coefficient variation of cluster size 0.22. We aimed to detect a minimum of a 25% absolute increase in behaviour in the intervention compared to the control arm. Thus with a significance level of 5% and 95% power, 15 clusters per arm, with a

minimum of 12 mothers per cluster was needed. Assuming loss to follow-up we intended to recruit 20 mothers within each village. In a sensitivity analysis, assuming a larger ICC of 0.1, the power (84%) remained reasonable.

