### **2.1.3 The population sample of mothers per village for 2 years evaluation data**

**(including additional variables in 2.1.1 and 2.1.2)**

We aim to select mothers who are currently weaning or have children who may have a combination of weaning and family food (E.g. 24-36month old children). As such some will be those who would not have been pregnant or had an infant at the time of the 4-days campaign visits or the 5th-month reminder.

For sampling frame, as with the 6-month follow-up the baseline list of children in the villages will be updated using the maternal-child health register and village health worker's list of children in each village. From these there will be 26 mothers chosen from each of the control and intervention villages. Sample size will be 23-26 mothers per cluster (as suppose to the target of 20 at the 6-month follow-up) because as indicated in the 6-month sample size calculation a minimum of 12 mothers per cluster of weaning children is needed (see above sample size for 6-month follow-up) but at 2 years we have 2 groups of mothers: new mothers and those who are mothers at the time of the 4-days campaign activities. (New mothers at 2-year follow-up are those with children 6-25month who will be eating weaning-food. Children aged 26-36 months will still, for the most part, be eating weaning-food at 2-year follow-up plus some of the family-food. Their mothers would have been pregnant during the 4-days campaign visits of the intervention in December to February 2014 and ready to wean at the 5th-month reminder visit. This population are the candidates most likely to *remember and practice* the hygienic behaviours while still *making* weaning-food during the 2-year assessment.) Therefore, we aim to have approximately 12 of each sub-group of mothers recruited. All individual mothers or main carers of children 6 to 36 months living in the village for a minimum of 2 years will be eligible for selection but mothers who are not available for cooking the child's weaning-food during the 2-year evaluation visit will be

excluded. (All mothers were available for the 6-month evaluation survey so we envisage very few or no mothers will be excluded).

To capture all these sub-groups of mothers, the selection of the mothers will be stratified as follows:

1. All mothers of children age 18 to 24 months will be chosen.
2. The rest of the mothers will be chosen according to the following formula:

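### Section 1.2.6: the stated inputs give about 99–99.8% power (stated 95%) and, at ICC 0.1, about 94–98% (stated 84%), so the basis of 12 mothers per cluster cannot be traced

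*Protocol*

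**What the plan says.** Protocol section 1.2.6 sets out the whole calculation in one paragraph.

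- **Control proportion:** 17 of 150 observed events, or 11.3%, from formative research. It covers four practices (reheating stored food, and hand washing with soap at three points), each measured the first time it occurred.
- **Clustering:** "we assumed an intra-cluster correlation coefficient (ICC) of 0.04", and "a coefficient variation of cluster size 0.22".
- **Target:** "We aimed to detect a minimum of a 25% absolute increase in behaviour in the intervention compared to the control arm".
- **Result:** "Thus with a significance level of 5% and 95% power, 15 clusters per arm", with a minimum of 12 mothers in each. The recruitment target was raised to 20 to allow for loss to follow-up.
- **Sensitivity:** "In a sensitivity analysis, assuming a larger ICC of 0.1, the power (84%) remained reasonable".

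Section 2.1.3 carries the result into the 2-year survey. It refers back to the 6-month calculation, says "a minimum of 12 mothers per cluster of weaning children is needed", and aims for roughly 12 mothers in each of two sub-groups within a total of 23 to 26 per village.

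**The concern.** Every input to the calculation is printed except the sidedness of the test, so the two powers can be checked directly. Going from 11.3% to 36.3% is a large difference for 180 mothers per arm with a modest ICC, and 95% looks low for it. The sensitivity figure looks further off: raising the ICC from 0.04 to 0.1 should not bring a design of this strength down to 84%.

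What is at stake is the traceability of the 12 per cluster. It is the only quantitative justification offered for the 2-year sample and its sub-groups. If the printed inputs do not lead to it, a reader cannot tell what difference the 2-year survey was sized to detect.

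A second mismatch adds to this. The primary outcome in section 1.2.5 and Table 1 is five behaviours over all opportunities in the observation period. The 11.3% leaves out the washing of pots and utensils and counts only first occurrences.

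**Working it through.** **Inputs** (section 1.2.6 unless noted): p1 = 17/150 = 0.1133; p2 = 0.1133 + 0.25 = 0.3633; k = 15 clusters per arm (also section 1.2.9); m = 12; CV = 0.22; ICC = 0.04 or 0.1; 5% significance. Sidedness is not stated; two-sided is assumed.

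**Step 1, design effect.** DE = 1 + ((1 + CV²)·m − 1)·ICC, with (1 + 0.0484)·12 = 12.5808.

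- ICC 0.04: 1 + 11.5808·0.04 = 1.463; effective n per arm = 180/1.463 = 123.0
- ICC 0.1: 1 + 11.5808·0.1 = 2.158; effective n per arm = 180/2.158 = 83.4

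**Step 2, power (unpooled normal formula).** p1(1−p1) + p2(1−p2) = 0.1005 + 0.2313 = 0.3318.

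- ICC 0.04: SE = √(0.3318/123.0) = 0.0519; 0.25/SE = 4.81; power = Φ(4.81 − 1.96) = 99.8%
- ICC 0.1: SE = √(0.3318/83.4) = 0.0631; 0.25/SE = 3.96; power = Φ(3.96 − 1.96) = 97.7%

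**Step 3, other formulas.** Same inputs, two-sided:

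| Formula | ICC 0.04 | ICC 0.1 |
|---|---|---|
| Stated in the protocol | 95% | 84% |
| Unpooled, normal | 99.8% | 97.7% |
| Pooled null variance, normal | 99.7% | 97.2% |
| Unpooled, t on 28 df | 99.6% | 96.9% |
| Unpooled, t, continuity correction | 99.4% | 95.4% |
| Pooled variance throughout, t, continuity correction | 99.0% | 93.6% |

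The last row is the most severe variant tried. A one-sided test moves power further up.

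**Step 4, the minimum cluster size.** For 95% power at ICC 0.04 and 15 clusters per arm, m = 6 gives DE = 1.212 and effective n = 90/1.212 = 74.3. Power is then 96.3% (unpooled), 95.5% (pooled) or 95.1% (unpooled with t). With 5 mothers the unpooled formula gives 93.5%. The most severe variant needs 8 (95.8%; 93.7% at 7). So 6 to 8 mothers suffice, depending on the formula, and not a minimum of 12.

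**Step 5, other readings of the text.**

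- 20 mothers per cluster: 99.98% and 98.9% (pooled), further from 84%.
- 25% as the final level, not the increase: 79.8% and 63.1% with 12 mothers, 90.3% and 71.1% with 20.
- 15 clusters in total: 91.2% and 77.4%, and this contradicts section 1.2.9.
- ICC at which 25 points with 12 mothers would give 84%: about 0.23 (pooled) to 0.25 (unpooled), not 0.1.

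**Step 6, what would give both stated powers.** Two sets of unstated inputs come close:

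- 18 points (11.3% to 29.3%), unpooled normal formula: 94.9% and 84.2%.
- 25 points centred on 50% (37.5% vs 62.5%), pooled variance, t and continuity correction: 95.6% and 84.3%.

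**The case against.** The strongest defence is that 99.8% satisfies a requirement of at least 95%, so 12 per cluster is a safe minimum for the stated 25 points and nobody is harmed by it. Much of this stands. The discrepancy is conservative, the 6-month survey is complete, and section 1.2.6 is reproduced mainly for reference. The defence does not reach the 84%, which is offered as a computed sensitivity result and not as a floor. Nor does it explain why 12 is called the number needed when 6 to 8 would do.

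A second defence is that the sponsor used another formula. The reference cited for the calculation is number 22, and the protocol's list ends at 17, so the formula cannot be identified. No standard variant applied to the printed inputs comes near 84%, however.

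A reader might infer that the trial was really sized for 18 points and that the text misprints the target. The documents do not support that. They never mention 18 points; the value is back-solved and depends on the formula (pooled with t, the same 18 points give 92.7% and 80.2%). A 25-point difference centred on 50% fits about as well, though it discards the stated 11.3%.

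A reader might also infer that a null 2-year result would be misjudged against 25 points. Section 1.2.11 commits to 95% confidence intervals, and such a result would be read from those.

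**Conclusion.** The stated figures do not follow from the stated inputs. Power for 25 points is about 99–99.8% at ICC 0.04 against a stated 95%, and about 94–98% at ICC 0.1 against a stated 84%. The minimum for 95% power at ICC 0.04 is about 6 to 8 mothers per cluster, not 12. The 84% is the clearer error; the 95% could be excused as a floor if it stood alone.

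This rests on a two-sided 5% test and a comparison of proportions on the effective sample size. It does not represent the Poisson model with offset that section 1.2.11 plans for the primary outcome.

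The error understates power, so it is no argument that either survey is too small. What fails is traceability: section 2.1.3 rests its sub-group numbers on a minimum that the printed calculation does not yield. The 11.3% is also not the control proportion of the primary outcome, so even the corrected powers describe a related quantity. For the same reason, detectable differences computed from 11.3% for the 2-year sample would be conditional figures only.

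**What to change.** Check the calculation file behind section 1.2.6, then do one of two things:

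1. Keep 11.3% and 25 points, and correct the powers (99.8% and 97.7% by the unpooled normal formula) and the minimum cluster size. Name the formula and the sidedness.
2. State the control proportion and target difference that actually gave 95% and 84%, with the formula.

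An 18-point target should not be written in unless the sponsor's own records show it.

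In either case, say in section 1.2.6 that the 11.3% covers four behaviours at first occurrence and why it was taken to stand for the five-behaviour outcome. In section 2.1.3, correct the claim that 12 per cluster is needed. Restate there the power or detectable difference for about 12 mothers per sub-group and for 23 to 26 overall, with the control proportion and ICC assumed.

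The cost is a rewording of two sections and a short recalculation. Enrolment does not change.
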